#### 1.5.2.3 Clinical efficacy data for AXA1125

1.5.2.3.1 Studies in NASH

Study AXA1125-002 was a 12-week, open-label, exploratory study of the safety and tolerability of

AXA1125 and the effect on liver structure and function for 12 weeks in subjects with NAFLD and

T2DM. Daily administration of AXA1125 22.6 g TID (67.8 g/day) up to 12 weeks in subjects with NAFLD and T2DM was safe and generally well tolerated. The effects of AXA1125 on key pathways implicated in the pathogenesis of NASH were explored in this open-label study. Lipotoxicity and insulin resistance are considered metabolic drivers of NAFLD. Administration of AXA1125 22.6 g TID up to 12 weeks in subjects with NAFLD and T2DM was associated with a decrease in mean liver fat content and from 18.0% at baseline to 13.4% at Week 12. Homeostatic Model Assessment of Insulin Resistance (HOMA-IR) also decreased from 7.4 at baseline to 4.9 at Week 12. In addition, there was a decrease in mean alanine aminotransferase (ALT) levels, as well as other blood biomarkers of inflammation, apoptosis, and fibrosis. The mean ALT was 47.3 U/L at baseline and decreased to 32.1 U/L (-10.2% relative change), and N-terminal type III collagen pro-peptide (Pro-C3), a measure of fibrogenesis, decreased from 21.6 ng/mL at baseline to 16.9 ng/mL (-19% relative change).

Overall, results from this pilot open-label food study showed directional consistency of change across several structural and functional biomarkers associated with liver health after

AXA1125 administration and provided support for a larger, randomized, placebo-controlled study of AXA1125.

Study AXA1125-003 was a 16-week, single-blind, randomized, placebo-controlled food study of the safety and tolerability of AXA1125 relative to placebo in subjects with NAFLD with and without T2DM. Daily administration of AXA1125 22.6 g BID (45.2 g/day) up to 16 weeks was safe and generally well tolerated. A larger mean absolute and relative reduction from baseline in liver fat by magnetic resonance imaging-proton density fat fraction (MRI-PDFF) was observed at Week 16 with AXA1125 compared with placebo. The relative reduction in MRI-PDFF was -5.74% for those subjects who received placebo and -22.8% for those who received AXA1125. At Week 16, a relative

reduction in liver fat by MRI-PDFF by ≥30% from baseline was observed in a numerically higher percentage of subjects who received AXA1125 (10/26 subjects, 38.5%) compared with placebo (1/12 subjects, 8.3%). This is considered to be a clinically relevant threshold as PDFF has been correlated with the NAFLD activity score (Jayakumar 2019, Caussy 2020). Reductions in MRI-PDFF have been associated with histologic improvement, including reductions in inflammation and ballooning, in NASH studies using obeticholic acid (Loomba 2020) and ezetimibe (Patel 2016). Improvements in measurements of insulin resistance, such as HOMA-IR and glycated hemoglobin (HbA1c), were also seen more consistently in the AXA1125 group. HOMA-IR decreased -4.369 in those who received AXA1125 and increased 0.720 in those who received placebo. HbA1c decreased, with an absolute change in HbA1c of -0.30 in the AXA1125 group and -0.17 in the placebo group.

As a measure of hepatic injury, the relative reduction in ALT from baseline was greater in subjects who received AXA1125 compared with placebo at Week 16. The ALT reduction was -14.4 U/L (-21.86% relative change) in the AXA1125 group and -8.9 U/L (-7.2% relative change) in the placebo group. A numerically higher percentage of subjects in the AXA1125 group had an absolute reduction

in ALT of ≥17 U/L from baseline (10/26 subjects [38.5%] in the AXA1125 group compared to 3/12 subjects [25%] in the placebo group]), which is a threshold that has been associated with 2-point improvement in NAFLD activity score on biopsy (Loomba 2019).

Biomarkers of fibrosis were shown to be reduced by the administration of AXA1125. At Week 16, greater absolute and relative reductions in Pro-C3 were noted in the AXA1125 group compared with placebo.

Of note, changes in liver structure, metabolic effects, and fibroinflammatory biomarkers were numerically larger in the subgroup of subjects with T2DM, which is a clinically important subgroup of subjects with NASH. In the T2DM subgroup, there were decreases in HOMA-IR, HbA1c, fasting insulin, and insulin AUC (0-120 minutes) following an oral glucose challenge that were more pronounced in the AXA1125 group than those observed in the placebo group.

1.5.2.3.2 Studies in PASC

No clinical studies of efficacy have been conducted in subjects with PASC. An interim look at the data from Cohort A indicated no association between baseline fatigue score and baseline PCr. Additionally, change in fatigue score did not correlate with change in PCr recovery rate utilizing bimodal scoring at Week 4. However, there was a statistically significant improvement in fatigue using CFQ-11 when assessed prior to 6MWT. Accordingly, CFQ-11 was determined to be an appropriate primary endpoint for the assessment of fatigue in Cohort B which includes patients who were considered screen-failures in Cohort A due to their PCr recovery rate constant (< 50 seconds), provided their CFQ-11 score is _≥8_ and they meet all the eligibility criteria.

## 1.6 Study Rationale

PASC is a chronic, multi-organ disease predominantly characterized by fatigue and muscle weakness (Lopez-Leon 2021) potentially leading to significant impacts on individuals’ QoL, as well as their ability to be productive members of society insofar as it affects ability to work. The fatigue symptoms that patients with PASC experience is similar to chronic fatigue syndrome (Komaroff and Lipkin 2021).

AAs are known to catalyze a broad range of functions, including cellular metabolism, anti-oxidative signaling, differentiation, and cellular homeostasis, among others, across different organ systems and are therefore positioned to impact multiple pathophysiologies in this complex, systemic disease. Supplementation of AAs as single agents or high-order combinations has been reported to improve fatigue and muscle weakness (Wolfe 2017) and is hypothesized to improve PASC-fatigue via modulation of mitochondrial metabolism, redox imbalance, inflammation, and vascular insufficiency. AXA1125 (33.9 g BID), an orally active mixture of AAs, has the potential to alleviate fatigue in subjects with PASC compared to placebo. Results from previous studies have shown changes in bioenergetic state of tissue with administration of AXA1125 (Jason et al 2011).

To assess fatigue, this study utilizes the 6-minute walk test (6MWT) and Chalder Fatigue scale, which have been successfully validated and used in previous studies on chronic fatigue syndrome (Mantha et al 2020).

This is a pilot study, and the primary objective is to assess the efficacy and mechanism of action of AXA1125.

An interim look at the data from Cohort A indicated no association between Baseline fatigue score and Baseline PCr. Additionally, statistically significant improvement in fatigue scores using CFQ-11 prior to 6MWT did not correlate with changes in PCr recovery rate utilizing bimodal scoring at Week 4. Accordingly, CFQ-11 was determined to be appropriate primary end-point for the assessment of fatigue in Cohort B.

Moreover, in order to assess the relationship between AXA1125 and functional status, and to obtain valuable information on understanding the relationship between PCr and CFQ-11 results and

AXA1125 responses, those subjects who were considered screen-failures in Cohort A, due to their PCr recovery rate constant (<50 seconds) provided their CFQ-11 Total score is _≥8_ and they meet all the eligibility criteria for the study, will be included in a Cohort B to receive treatment for 4 weeks.

The efficacy endpoints for Cohort B include the change from Baseline at Week 4 in subjects’ fatigue score as assessed by CFQ-11 before 6MWT, which will be evaluated at Screening, Baseline, and End of Treatment or Early-Term. CFQ-11 will also be assessed at Day 14 (without 6MWT). Additional end-points for assessment of functional status, safety, and tolerability will be collected.

## 1.7 Benefit-Risk Assessment

PASC is a serious disease, potentially leading to significant impacts on individuals’ QoL, as well as their ability to be productive members of society insofar as it affects ability to work.

Improvements in mitochondrial bioenergetics have been observed in in vitro studies. The proposed dose is well supported by published literature of its constituents, including the clinical and nonclinical safety of its constituent AAs, and the clinical safety data available for AXA1125 across 3 completed studies and 3 ongoing studies for which preliminary data are available for 2 of the studies. Historical data have amply demonstrated the safety and tolerability of AAs, including in mixtures containing multiple AAs that have previously been approved as drugs. In cases where AEs were reported in past studies, they tended to be mild and transient gastrointestinal AEs, which were monitorable and generally clinically nonsignificant. AEs observed in short-term studies of AXA1125 have also shown a pattern of mild and transient gastrointestinal AEs. Thus, the in vitro findings and safety data for AXA1125 constituent AAs support a positive benefit-risk assessment for the use of AXA1125 in patients with PASC.

The safety and efficacy of AXA1125 has been evaluated in over 100 subjects as an amino acid food product. Studies in healthy volunteers and subjects with NASH are ongoing. AXA1125 has been found to be safe and well tolerated in doses up to 45.2 g/day AXA1125 for 16 weeks or 67.8 g/day AXA1125 for up to 12 weeks. No serious or related adverse reactions were identified by Axcella. Risks to subjects will be minimized by adherence to the eligibility criteria, close clinical monitoring, and monitoring of AEs.

To date, the cumulative data support the selection of doses of AXA1125 up to 67.8 g/day, which provides an optimal benefit-risk profile for evaluation of efficacy and safety.

Thus, the clinical efficacy and safety data for AXA1125 constituent AAs support a positive benefit-risk assessment for the use of AXA1125 in patients with PASC.

# 2 OBJECTIVES AND ENDPOINTS

## 2.1 Study Objectives – Cohort A

### 2.1.1 Primary objective

The primary objective is to:

• Assess the impact of AXA1125 on muscle function (metabolism) following exercise

### 2.1.2 Secondary objective

The secondary objectives are to:

- Assess the relationship between AXA1125 and functional status
- Assess the safety and tolerability of AXA1125

### 2.1.3 Exploratory objectives

The exploratory objectives are to:

- Obtain additional insights into the mechanism of action of AXA1125
- Obtain baseline AA profile in subjects with PASC

## 2.2 Study Objectives – Cohort B

- Assess the relationship between AXA1125 and functional status
- Assess the safety and tolerability of AXA1125

## 2.3 Study Endpoints

### 2.3.1 Efficacy endpoints – Cohort A

#### 2.3.1.1 Primary efficacy endpoint

The primary efficacy endpoint is:

• The mean change from baseline at Week 4 in the phosphocreatine (PCr) recovery rate following moderate exercise, as assessed by 31P-magnetic resonance spectroscopy (MRS)

#### 2.3.1.2 Secondary efficacy endpoints

The secondary efficacy endpoints are:

- Absolute and relative change from baseline in PCr recovery rate as assessed by phosphorus magnetic resonance spectroscopy (31P-MRS) at Week 4
- The proportion of subjects with improvement in PCr recovery rate at Week 4
- Absolute and relative change from baseline in serum lactate level after a 6MWT at Week 4
- The proportion of subjects with serum lactate level ≤3 mmol/L after a 6MWT at Week 4
- The proportion of subjects with a decrease in venous serum lactate level from baseline after a 6MWT at Week 4
- Change from baseline in distance traveled during a 6MWT at Week 4
- Change from baseline in subjects’ fatigue score as assessed by Chalder Fatigue Questionnaire (CFQ)-11 (by Bimodal Scoring) before and after a 6MWT at Week 4 and at Day 14 (without 6MWT)
- The proportion of subjects with an improvement in fatigue score as assessed by CFQ-11 before and after a 6MWT at Week 4

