###### Cohort A Only

• an elevated PCr recovery rate constant following moderate exercise on 31P-MRS (τ_PCr_ ≥50 seconds); and

Note: Documented 31P-MRS within 3 months of Screening and after 3 months of acute COVID-19 infection is acceptable. If a historical 31P-MRS has been used to determine eligibility, then 31P-MRS should be repeated within 1 month prior to Day 1 (ie, during the Screening Period) to confirm eligibility and establish baseline.

1. Other than PASC, a subject must be in good health without other significant medical or not well controlled medical or psychiatric conditions. Allowable conditions include mild hypertension,

dyslipidemia, pre-diabetes defined as HbA1c ≤ 6.0%, and/or asthma (mild and not requiring chronic daily treatment). Subjects who are treated for these conditions must be well controlled on a stable regimen (lifestyle modifications and/or medications), for at least 3 months prior to Screening and anticipate no significant alterations to these regimens for the duration of the study. However, doses of certain medications (eg, statins, antihypertensives) used to treat stable chronic conditions may be modified during the study for safety or tolerability issues, if needed at the discretion of the Principal Investigator (PI).

Note: A history of treated hepatitis C virus (HCV) infection is allowed, provided that a negative hepatitis C viral load has been documented at ≥12 weeks after the cessation of hepatitis C treatment. Historical medical record or testing to ensure a negative viral load may be permitted during the Screening Period. HCV ribonucleic acid will be tested in all subjects, including subjects with a history of treated HCV infection or with positive HCV antibody at Screening, provided that a negative hepatitis C viral load has not been documented at ≥12 weeks after the cessation of hepatitis C treatment.

1. A female subject must meet any one of the following criteria:
   1. Surgically sterile
   2. Postmenopausal with ≥12 months of amenorrhea without an alternate medical cause
   3. Follicle-stimulating hormone (FSH) level consistent with postmenopausal state if amenorrheic for <12 months or if <55 years of age

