## 4.2 Exclusion Criteria (Cohort A and B)

A subject will be excluded from the study if **any** of the following criteria are met:

1. Other than PASC, have an explanation for fatigue. This includes but is not limited to hypothyroidism; chronic cardiovascular, neurological, endocrinological, or peripheral vascular disease; history of major depression; clinically significant anemia; chronic liver disease; rheumatologic diseases requiring treatment with steroids or immunosuppressants; or other cause of neuromuscular disease such as muscular dystrophy.
2. Other than PASC, a history or presence of an uncontrolled, clinically significant disease including:
   - Type 1 or Type 2 diabetes mellitus
   - A medical condition that may interfere with absorption of the study drug, including but not limited to resection of any part of the gastrointestinal tract, gastric or intestinal bypass, any bariatric surgery, or inflammatory bowel disease
3. Meet any of the following during physical exam assessment:
   - Resting O_2_ saturation <95% on room air
   - Body mass index (BMI) of <18.5 or >35
   - Clinically significant abnormality on echocardiogram (to rule out abnormal cardiac function or elevated pulmonary artery pressure)
   - Is pregnant (if female) or lactating
4. Meet any of the following laboratory parameters:
   - Serum B-type natriuretic peptide (NT-proBNP) >400 pg/mL
   - Total bilirubin >1.3 mg/dL (>22.23 umol/L) or direct bilirubin >0.40 mg/dL (>6.84 umol/L) unless with a history of Gilbert’s syndrome
   - Aspartate aminotransferase (AST) or ALT >3 × upper limit of normal (ULN) AST >126 IU/L; ALT >135 IU/L
   - HbA1c >6.0%
   - Human immunodeficiency virus (HIV)-1 or -2 positive
   - eGFR <60 mL/min/1.73 m2 calculated using the Chronic Kidney Disease Epidemiology Collaboration equation
   - Positive for hepatitis B surface antigen (hBsAg), HCV antibody, or HIV antibody
5. Have a medical history that includes any of the following:
   - Non-invasive or invasive ventilatory support for COVID-19
   - Intensive care unit or other high dependency unit admission for COVID-19
   - Hospitalization for >1 week for COVID-19 without intubation
   - Planned or prior organ transplant

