### 6.8.4 Serum Lactate Test (Cohort A Only)

A serum lactate level that measures the amount of lactic acid in the body will be obtained at Day 1 and EOT/ET (Visit 4).

Also in association with moderate exercise, capillary blood lactate level is to be measured by earlobe puncture just before starting, immediately after and 5, 10, 20, and 30 minutes after the 6MWT. Detailed instructions will be provided in the Laboratory Manual.

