### 7.4.7 Efficacy analyses (Cohort A and B)

#### 7.4.7.1 Primary and key secondary efficacy endpoint analyses

The categorical endpoints will be analyzed using the Chi-square test. Subgroup analyses, such as by gender, may be performed.

Continuous endpoints will be analyzed using the analysis of covariance models adjusted for the baseline value. Mixed model repeated measures models will be applied as sensitivity analyses.

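### The Week 4 lactate status endpoint (≤3 mmol/L) counts subjects already at or below the cut at Day 1, and the stated unadjusted chi-square test makes no use of the Day 1 value

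*Protocol*

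**What the plan says.** Section 2.3.1.2, repeated in the synopsis, gives eight secondary efficacy endpoints for Cohort A, three of them on lactate. One is how far post-walk lactate has moved since baseline, in absolute and in relative terms. Another is the share of subjects whose venous value has fallen since baseline. The one at issue here is "The proportion of subjects with serum lactate level ≤3 mmol/L after a 6MWT at Week 4", and it alone makes no reference to baseline.

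Eligibility for Cohort A rests on "an elevated PCr recovery rate constant following moderate exercise on 31P-MRS" (at least 50 seconds) and a CFQ-11 total score of at least 8. The laboratory exclusions in section 4.2 contain no lactate limit.

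Section 6.8.4 schedules serum lactate at Day 1 and at the end-of-treatment or early-termination visit, and capillary lactate at fixed times around the 6MWT.

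For analysis, section 7.4.7.1 says: "The categorical endpoints will be analyzed using the Chi-square test". For endpoints measured on a continuous scale, the same section prescribes analysis of covariance with the baseline value as covariate.

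**The concern.** A subject with 2.0 mmol/L after the Day 1 walk and 2.6 mmol/L after the Week 4 walk meets the endpoint although lactate rose. Such subjects add the same amount to both arms in expectation. They pull the two proportions together and add noise.

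An unadjusted chi-square test cannot separate them from subjects who crossed the cut during treatment. Nor does it correct a chance difference between arms in the number starting at or below 3 mmol/L. Continuous endpoints are adjusted for baseline under the same section, and this binary endpoint is not. At stake is the precision and readability of one secondary comparison, which is tested at the two-sided 0.05 level like every other.

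**Working it through.** **Inputs from the protocol.** About 20 subjects per arm, 1:1 allocation, 20% dropout (sections 7.1 and 7.4.2). The protocol gives no power or event rate for any lactate endpoint. Its one sample size figure concerns PCr recovery, and it reproduces: n per arm = 2 × (1.960 + 0.842)² × (10/10)² = 15.7, rounded up to 16, so 32 evaluable and 32/0.80 = 40 enrolled. It is used here only for the arm sizes.

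**Assumed inputs, none of them in the protocol.** Share b already ≤3 mmol/L at Day 1: 30, 50 or 70%. Probability s that such a subject is still ≤3 at Week 4: 90% in both arms. Conversion c among subjects starting >3: 60% active, 20% placebo.

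**Step 1, dilution.** The expected proportion meeting the endpoint in an arm is b·s + (1 − b)·c, so the difference between arms is (1 − b) × 40 points.

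| b | Active | Placebo | Difference |
|---|---|---|---|
| 30% | 0.27 + 0.42 = 69% | 0.27 + 0.14 = 41% | 28 points |
| 50% | 0.45 + 0.30 = 75% | 0.45 + 0.10 = 55% | 20 points |
| 70% | 0.63 + 0.18 = 81% | 0.63 + 0.06 = 69% | 12 points |

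At b = 10% the same formula gives 63% versus 27%, a difference of 36 points, so the dilution is small if few subjects start below the cut.

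**Step 2, how much of the count is starting status.** Among subjects meeting the endpoint, the share already ≤3 at Day 1 is b·s divided by the arm's proportion. At b = 10% it is 0.09/0.63 = 14% active and 0.09/0.27 = 33% placebo. At b = 50% it is 0.45/0.75 = 60% and 0.45/0.55 = 82%. The answer turns entirely on b.

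**Step 3, chance imbalance.** With independent binomial counts of size 20 in each arm, the probability that the arms differ by at least 3 subjects (15 points) in Day 1 status is 0.39, 0.43 and 0.39 at b = 30, 50 and 70%. Either arm is equally likely to be favoured.

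**Step 4, power.** Simulated trials under these assumptions, two-sided 5%:

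| b | Chi-square, 20 per arm | Cochran-Mantel-Haenszel by Day 1 status, 20 per arm |
|---|---|---|
| 30% | 41% | 53% |
| 50% | 27% | 34% |
| 70% | 14% | 17% |

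At 16 per arm, after the protocol's own dropout allowance, the figures are about 37/23/13% for chi-square and 44 to 45/28/14% for the stratified test. With no treatment effect, both tests reject about 5% of the time.

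**The case against.** The case for leaving the endpoint alone is fair, and much of it stands.

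- **Baseline is not ignored for lactate.** The subject going from 2.0 to 2.6 fails the decrease endpoint, and the change endpoint is baseline-adjusted. How many subjects are at or below a fixed level at Week 4 is a legitimate, separate question. This stands, and it is why the endpoint should be kept.
- **Randomisation balances Day 1 status in expectation.** A reader might infer that the comparison is biased. The documents do not support that: chance imbalance is part of the variation the test allows for, and the type I error holds. What remains is lost precision.
- **The size is unknown.** A reader might infer that the endpoint measures starting status as much as response. That needs a large share already ≤3 mmol/L, and the protocol gives no baseline lactate data. At a 10% share the difference is still 36 of 40 points.
- **Redefining it as conversion among subjects >3 at Day 1 is not clearly better.** It leaves about 14, 10 or 6 subjects per arm, drops those who worsen across the cut, and still counts a fall from 7 to 3.2 mmol/L as a failure. Its power is about 61/47/29% by chi-square, but 49/35/15% by Fisher's exact test, which suits such numbers better.
- **The SAP may refine the analysis.** Section 7.4.1 leaves detailed methods to it, and randomisation details are left to a separate plan. So nothing is made here of absent stratification at randomisation. The chi-square test, however, is named in the protocol, and an SAP that follows the text inherits it.

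**Conclusion.** The point holds in limited form. By its wording the endpoint combines subjects who were already ≤3 mmol/L with those who reached that level on treatment, and the stated test makes no use of a Day 1 value that the plan collects. The consequence is reduced precision and uncorrected chance imbalance.

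Under the assumed rates, stratifying gains 12, 7 and 3 points of power at baseline shares of 30, 50 and 70%. No version is well powered, because the trial was sized on PCr recovery. The numbers rest wholly on assumed lactate rates and show only the direction and rough scale. Priority is low: this is one of eight listed secondary endpoints in a pilot, beside two lactate endpoints that use baseline.

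**What to change.** Keep the endpoint and describe it as status at Week 4. In place of the unadjusted chi-square test, compare the arms with a test stratified by Day 1 post-walk status (≤3 or >3 mmol/L), either Cochran-Mantel-Haenszel or an exact stratified test. A logistic model with Day 1 post-walk lactate as covariate is the alternative.

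Add a descriptive table by arm of Week 4 status against Day 1 status, including conversion among subjects >3 mmol/L at Day 1. State which Day 1 sample is used and match it to the Week 4 sample in type and timing: section 6.8.4 times the capillary samples relative to the walk but does not time the serum draw.

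The cost is one changed test and one table, with no new data. Strata will be small, so an exact version may give back some of the gain in power.
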